### Participants

The inclusion criteria are as follows: (1) age 18–80 years old. (2) first unilateral stroke (cerebral infarction, primary intracerebral hemorrhage, subarachnoid hemorrhage) confirmed by MRI or CT within 6 months before enrolment. (3) Perceptible muscle spasticity with MAS score >1. (4) Severe motor impairment with the Fugl-Meyer Assessment of Upper Extremity (FMA-UE) score 0–35 (9, 26). (5) Failure to induce MEP in the upper extremity of the hemiplegic side (27, 28). (6) Mini-Mental State Examination (MMSE) score ≥ 22 and compliance with the interventions. (7) sign the informed consent.

The exclusion criteria are as follows: (1) more than one stroke (patients with previous transient ischemic attack could participate), bilateral cerebral hemisphere lesion. (2) history of seizures or seizures after stroke, severe skull fracture. (3) conditions unsuitable for TBS (29), e.g., intracranial implants, cardiac pacemakers or pregnancy, implanted drug pumps, etc. (4) Medications (such as lignocaine, penicillins, cephalosporins, amphotericin, tricyclics, selective serotonin reuptake inhibitors, azatadine, aminophylline, bupropion, imipramine, clozapine, olanzapine, etc.) that may lower the seizure threshold have been used continuously for nearly 3 months. (5) serious impairments of heart, lung, liver, kidney, and other organs, cannot tolerate training. (6) participation in other spasticity rehabilitation studies.

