### Procedure

The study will consist of four phases: (1) A baseline assessment involving clinical scales (MAS and FMA-UE) and DTI before the stimulation sessions; (2) Comprehensive rehabilitation, and the corresponding cTBS interventions will be provided once a day, 5 times a week for 4 weeks. Neurophysiological assessments such as H reflex, MEP and SR will be collected before and after the first cTBS treatment at this phase; (3) Post-intervention (4 weeks) clinical, neurophysiological and DTI assessment; (4) Follow-up (8 weeks) clinical and neurophysiological assessment. Figure 1 shows the flow diagram of this study.

All stroke patients will receive a routine treatment programme including rehabilitation, medication, multidisciplinary therapy. The patient's rehabilitation included various forms of physical and occupational therapy, ~3 to 4 hours a day, 5 days a week, for 4 weeks. The intensity of active training will be appropriately adjusted according to the patient's tolerance. At the same time, an additional cTBS treatment will be provided for those participants for 4 weeks, once a day. Each patient's cTBS intervention will be performed by the same therapist.

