### Outcome measurements

The primary outcomes are MAS and FMA-UE. Changes before and after the 4 weeks of treatment will be used as the primary measure to assess improvement in spasticity and abnormal movement synergies (9). And the secondary outcomes are results from neurophysiological examinations including H reflex, M response, MEP and SR, and changes of neuroimaging with DTI.

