### Sample size calculation

Sample size is estimated through software G^*^Power 3.1 (50). We used MAS as the primary outcome for the calculation of the effect size. It is determined to be 12 per group based on a power of 0.8 with α level at 0.05. According to a previous study (21), effect size *d* = 0.53 was calculated based on the difference in MAS score from their main research results. Through conversion, the effect size *f* used in our study is about 0.25. Repeated measures correlation in our study is set at 0.5 to detect a moderate within-between effect of Conhen's *f* = 0.25. Considering a drop-out rate of 20%, we aim to recruit totally 45 stroke subjects.

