### Statistical analysis

The SPSS 21.0 program will be used for all statistical analysis and the significance level set for all the analysis will be *P* ≤ 0.05. The Shapiro-Wilk test will be used (*P* > 0.05) to check normality. In this study, Continuous variables will be expressed as mean with standard deviation and median for non-normal distributions and categorical variables will be presented as percentage or frequencies. Between the three groups, data will be first compared using Student's *t*-test for continuous variables and the chi-square or Fisher's exact tests for categorical variables. Appropriate metrics will be processed further using repeated measures ANOVA. Bonferroni correction method and False Discovery Rate <5% will be considered for multiple comparisons. All analyses will be done with the intention to treat principle, and missing data will be estimated using multiple imputation. The mean comparisons for related outcomes in two different moments will be studied with the Wilcoxon-signed rank test. The major strategy for dealing with missing data will be a sensitivity analysis and weighted estimating equations.

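### No between-arm test is assigned to the primary week-4 change in MAS and FMA-UE, and none of the methods named adjusts for the baseline score

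*Protocol article*

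**What the plan says.** Under Outcome measurements, MAS and FMA-UE are the primary outcomes, and the measure is a two-point one: "Changes before and after the 4 weeks of treatment will be used as the primary measure". Table 1 and Clinical assessments place both scales at baseline, week 4 and week 8.

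Statistical analysis names three kinds of method without linking any of them to that measure:

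- a between-group comparison: "Between the three groups, data will be first compared using Student's" *t*-test for continuous variables, with chi-square or Fisher's exact tests for categorical ones;
- a longitudinal model: "Appropriate metrics will be processed further using repeated measures ANOVA", with metrics, factors and covariates unstated;
- a paired test: "The mean comparisons for related outcomes in two different moments will be studied with the Wilcoxon-signed rank test".

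Sample size calculation rests on a group-by-time effect: "Repeated measures correlation in our study is set at 0.5 to detect a moderate within-between effect of Conhen's" *f* = 0.25. The underlying *d* = 0.53 "was calculated based on the difference in MAS score from their main research results" of a previous study.

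**The concern.** The trial's question is comparative: cPMA against sham, and against cM1. The sentence whose wording comes closest to the primary measure names a test with no arm term, and one that does not compare means either.

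A within-arm p-value is a weak guide to treatment effect here. Patients are within 6 months of stroke and enter with "Perceptible muscle spasticity with MAS score >1". All arms get the same background programme: "The patient's rehabilitation included various forms of physical and occupational therapy, ~3 to 4 hours a day, 5 days a week, for 4 weeks". Change unrelated to cTBS is therefore plausible in every arm. If within-arm tests were used for inference, a significant result in cPMA and a non-significant one in sham could arise without any treatment effect.

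The second issue is precision. Baseline MAS and FMA-UE are collected in everyone, yet no method as named adjusts for them. With 12 to 15 patients per arm, that gives away information already in hand.

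**Working it through.** **Inputs from the protocol.** Three arms, 1:1:1; *f* = 0.25; *d* = 0.53; correlation ρ = 0.5; α = 0.05; power 0.80; 12 per group; 20% dropout; 45 in total; primary scales at three visits.

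**1. Reproducing the stated sample size.** For the within-between interaction, λ = f²·N·m/(1−ρ), with (k−1)(m−1) and (N−k)(m−1) degrees of freedom. With k = 3, m = 3 and N = 36:

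- λ = 0.0625 × 36 × 3 / 0.5 = 13.5, on 4 and 66 df; power is 0.82.
- 36 / (1 − 0.20) = 45.

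The stated figures reproduce, using all three visits.

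**2. The same calculation on the primary measure.** With baseline and week 4 only (m = 2), λ = 0.0625 × 36 × 2 / 0.5 = 9.0 on 2 and 33 df. Power at N = 36 is 0.73, and 80% needs N = 42 (14 per group). At m = 2 the interaction test is identical to a one-way ANOVA on change scores.

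**3. Variance of the week-4 contrast**, in units of the raw variance σ²:

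| Method | Formula | ρ = 0.5 | ρ = 0.7 |
|---|---|---|---|
| Change score | 2(1−ρ) | 1.00 | 0.60 |
| ANCOVA | 1−ρ² | 0.75 | 0.51 |
| Saving | (1−ρ)/2 | 25% | 15% |

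The saving is 35% at ρ = 0.3 and 10% at ρ = 0.8. Estimating the slope multiplies the ANCOVA variance by about 1 + 1/(N−5). At N = 36 that gives 0.75 × (1 + 1/31) = 0.774, and at N = 45, 0.75 × (1 + 1/40) = 0.769. The net saving at ρ = 0.5 is therefore about 23%. Before that cost, 15 per arm with ANCOVA is worth 15 / 0.75 = 20 per arm with change scores.

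**4. Pairwise power.** Reading *d* = 0.53 in raw-SD units, the ANCOVA-scale effect is 0.53/√0.75 = 0.612. Two-sided t-test at 0.05:

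| Per arm | Change score | ANCOVA |
|---|---|---|
| 12 | 0.24 | 0.30 |
| 15 | 0.29 | 0.37 |

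These figures are not on the same footing as the 0.73 in step 2. There, λ = 9.0 = 36 × 0.5², so an interaction *f* of 0.25 at ρ = 0.5 amounts to *f* = 0.50 for a one-way ANOVA on change. That is a larger effect than a pairwise raw-SD difference of 0.53.

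**5. If within-arm signed-rank tests were used for inference.** Simulation with 12 per arm, normal changes, no difference between arms, and an assumed common change in every arm in units of the SD of change. With independent arms that have the same within-arm rejection probability p, the chance of significance in cPMA and not in sham is p(1−p), which cannot exceed 25%.

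| Common change (SD) | cPMA significant, sham not |
|---|---|
| 0 | about 4% |
| 0.3 | 12% |
| 0.5 | 22% |
| 0.6 | 25% |
| 0.8 | 22% |

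**The case against.** A reader might infer that the primary measure is to be decided by within-group Wilcoxon tests. The article does not say so. The signed-rank sentence mentions neither MAS nor FMA-UE, and it fits other measures at least as well: DTI is done exactly twice, and the neurophysiology has a pair of readings around the first session. Between-group methods are listed, and the trial is sized on a group-by-time effect. That objection stands, so the defect is an unassigned primary test.

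A reader might also class the repeated-measures ANOVA as the wrong contrast. It is not: in a randomised trial its interaction is a valid comparison of arms. What can be said against it is lack of focus over three visits and lost efficiency over two.

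The false-signal rates depend on an assumed common improvement, and the article gives some reason for doubt. Its Introduction says spasticity in some severely injured patients develops in the opposite direction to the usual improvement. The rates near 25% are the mathematical ceiling, and at zero common change the rate is about 4%. They show what within-arm inference would risk and do not predict how the sponsor will report.

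Finally, the article is condensed, and covariates and planned contrasts may be set out in a fuller plan. That lowers the weight of the missing covariate. It does not alter the fact that the methods section, where it does name methods, leaves the primary change without a deciding between-arm test.

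**Conclusion.** The point holds as one of specification and efficiency. The primary measure is the week-4 change, no test is assigned to it, the only test named for two moments cannot compare arms, and the between-group methods are named without baseline adjustment.

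At ρ = 0.5, ANCOVA reduces residual variance by 25% relative to change scores, or about 23% net of estimating the slope. That ρ is the plan's assumption, and the gain shrinks as it rises. The saving is not measured against the signed-rank test or the three-visit interaction. The gain in pairwise power is 6 to 8 percentage points and does not rescue it: power stays below 0.40 at 15 per arm if *d* = 0.53 is in raw-SD units. The change is still worth making, because it settles which comparison decides the trial and uses data already collected.

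**What to change.** For each primary outcome, make the primary analysis a between-arm comparison at week 4 adjusted for the baseline value: ANCOVA with arm at three levels plus baseline score, reporting cPMA minus sham with its 95% CI. Report within-group signed-rank results as descriptive only.

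For MAS, first define a single score. The scale is recorded separately for four muscle groups and includes a 1+ grade, so state how the groups are combined and what numeric value 1+ takes. Because MAS is ordinal, add a rank-based or ordinal model with the same terms as a sensitivity analysis; with 12 to 15 per arm, sparse categories may limit a proportional-odds fit.

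No extra data collection is needed, since both scales are measured at baseline in all patients. There are two costs: the MAS summary must be settled before unblinding, and the primary test will no longer match the three-visit interaction behind the sample size, so that section should be restated on the week-4 contrast.

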## Discussion

The motor recovery after stroke follows a basically predictable pattern, from flaccid, spastic to recovered (4, 10). In patients with severe stroke, motor function may be arrested at a certain stage limited by spasticity for a long time in the process of motor recovery (4), which is a thorny problem in the rehabilitation process. Motor rehabilitation relies on a complex combination of spontaneous recovery and motor learning to promote neural plasticity (11, 51). The spinal plastic change relates to the severity of cortical damage and has a time-limited window, almost entirely in the first weeks (52, 53). The anatomical structure determines that in patients with severe stroke, CST is more vulnerable to damage, ultimately leading to the facilitatory medial RST being unopposed and independent of cortical control (13), which plays a significant role in spasticity. Spasticity reflects a phenomenon of maladaptive neuroplasticity in motor control pathways (12), and can easily develop if there is not appropriate intervention to regulate in the course of recovery (54).

Non-invasive magnetic stimulation is a promising therapy option for modulating neural plasticity, but the undetected MEP (27) and the extensive recombination of the cerebral cortex (55) after severe stroke lead to doubtful targeting in the cortex for treatment. Although there is weak-grade evidence to support that the contralesional TMS targeting cM1 improves post-stroke spasticity, the effect is inconclusive (54). Exploring the spasticity mechanism in severe stroke patients may be more helpful to obtain optimized intervention targets and clarify the effect of this non-invasive treatment.

As mentioned previously, spasticity is thought to be a top-down manifestation resulting from hyperexcitability of the advance central PMA and its corresponding descending pathway of medial RST (12). This study will compare the acute and short-term effects of cTBS over cPMA and M1 in severe stroke patients. Moreover, we aim to demonstrate that the hyperexcitable cPMA after stroke is the cortical manifestation causing spasticity, and reducing the hyperexcitability of cPMA may help to down regulating the excitability mRST of hemiplegic side and to facilitate adaptive neuroplasticity of RST in spasticity relief and motor recovery.

Several characteristics distinguish this study from previous reports. Firstly, it is the first clinical study that TBS improves spasticity by regulating the neuroplasticity of cPMA and mRST. The results will verify the relationship between spasticity, cPMA and mRST, and provide theoretical and practical support for effective improvement of spasticity. Otherwise, the changes of neuroplasticity and spasticity after stroke will be evaluated objectively and comprehensively from clinical, electrophysiological and neuroimaging perspectives. In this study, we use the FMA-UE scale to monitor the recovery course of the upper extremity's motor function (56). Moreover, subsections and items of FMA-UE such as synergy or out-of-synergy movements can roughly reveal the pathways (CST/RST) that patients currently dominate their motor and spastic recovery (9). Some personalized rehabilitation decisions based on this feature may help develop more effective treatment plans. DTI biomarkers of CST have been considered as predictors of motor recovery (48). In this study, DTI will be used to evaluate the neuroplasticity changes of both RST (47) and CST (48) in post-stroke spasticity. The results will be used to further clarify the dynamic competitive relationship between the both (9). We expect that the results of this study can provide powerful support for the application of TBS neuromodulation in improving spasticity, and we may supplement targeted training [motor training, auditory stimulation training (57), etc.] in different stages of motor recovery in the near future, so that stroke patients can reasonably utilize CST and RST pathways to facilitate motor function recovery.

## Ethics statement

The studies involving human participants were reviewed and approved by Institutional Ethical Committee of Tongji Hospital. The patients/participants provided their written informed consent to participate in this study.

## Abbreviations

Abbreviations: CST: corticospinal tract
RST: reticulospinal tract
cPMA: contralesional premotor area
cM1: contralesional primary motor cortex
mRST: the medial reticulospinal tract
LTD: long-term depression
FMA-UE: Fugl-Meyer Assessment of Upper Extremity
MEP: motor evoked potential
SR: startle reflex
MAS: Modified Ashworth scale
DTI: Diffusion tensor imaging
Hslp/Mslp: the ratio of the slope of H and M-waves
Hmax/Mmax: the ratio of the maximum of H and M-waves
RN: red nucleus.
